## Abstract

**Background:**

Data from interventional studies suggest that a peritoneal flap after pelvic lymph node dissection (LND) during laparoscopic, robotic-assisted radical prostatectomy (RARP) may reduce the rate of symptomatic lymphoceles in transperitoneal approach. However, most of these studies are not conducted in a randomized controlled fashion, thus limiting their scientific value. A recent prospective, randomized, controlled trial (RCT) did not show superiority of a peritoneal flap while further trials are lacking. Therefore, the aim of the presented RCT will be to show that creating a peritoneal flap decreases the rate of symptomatic lymphoceles compared to the current standard procedure without creation of a flap.

**Methods/design:**

PELYCAN is a parallel-group, patient- and assessor-blinded, phase III, adaptive randomized controlled superiority trial. Men with histologically confirmed prostate cancer who undergo transperitoneal RARP with pelvic LND will be randomly assigned in a 1:1 ratio to two groups—either with creating a peritoneal flap (PELYCAN) or without creating a peritoneal flap (control). Sample size calculation yielded a sample size of 300 with a planned interim analysis after 120 patients, which will be performed by an independent statistician. This provides a possibility for early stopping or sample size recalculation.

Patients will be stratified for contributing factors for the development of postoperative lymphoceles. The primary outcome measure will be the rate of symptomatic lymphoceles in both groups within 6 months postoperatively. Patients and assessors will be blinded for the intervention until the end of the follow-up period of 6 months. The surgeon will be informed about the randomization result after performance of vesicourethral anastomosis. Secondary outcome measures include asymptomatic lymphoceles at the time of discharge and within 6 months of follow-up, postoperative complications, mortality, re-admission rate, and quality of life assessed by the EORTC QLQ-C30 questionnaire.

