### Outcomes

#### Primary endpoint

Difference between the two treatment arms in proportions of patients showing a symptomatic lymphocele within 6 months postoperatively. A symptomatic lymphocele is defined as sonographically detectable fluid accumulation in the area of the previously performed LND with the need of an interventional or operative therapy due to one of the following symptoms
Lower abdominal pain (after ruling out differential diagnosis)Deep vein thrombosis/leg swelling/lymph drainage problemsSuperinfection (fever/sepsis)

Data will be collected directly from the patients. These data will be complemented by the information gathered from the out-patient urologists, who treat the patients in an ambulant setting and perform their oncological follow-up.

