#### Secondary outcome measures

For the secondary endpoint asymptomatic lymphocele at the time of discharge, ultrasonography will be performed by the assessors at the day of discharge. The assessors are blinded to the treatment group. Performing ultrasonography reflects the department’s standard of care. Asymptomatic lymphocele is defined as a sonographically detectable accumulation of fluid without symptoms. Furthermore, we will conduct a follow-up 6 months postoperatively. We will contact the patient directly. All patients gave informed written consent to be contacted. Lymphocele symptoms (pain, superinfection, deep vein thrombosis, or need for drainage insertion) will be assessed separately. Further secondary endpoints include:
Rates of asymptomatic lymphoceles at the time of dischargeThe combined endpoint of asymptomatic lymphoceles at the time of discharge and symptomatic lymphocelesQuality of Life (QLQ-C30, EORTC)Rehospitalization rate within 6 months after surgical treatmentRe-intervention rateLymphedema and/or erysipelasDeep vein thrombosisPerioperative parameters (operating time, complication (Clavien-Dindo & Comprehensive Complication Index, blood loss)Length of hospital stay

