**Assessments**							
Pre-existing medical conditions	AD	x					
Medication	AD	x				x	
Abdominal ultrasound	AD	x				x	
Quality of life (QLQ-C30, EORTC)	AD, PU	x					x
Lymphocele (symptomatic/asymptomatic)	WD, PU					x	x
Lymphocele symptoms	WD, PU					x	x
Lymphedema/erysipelas	PU						x
Rehospitalization	PU						x

*Enroll* enrolment, *INT* intervention, *SC* study coordinator, *AD* admission doctor, *OS* operating surgeon, *WD* ward doctor, *PU* private urologist

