##### Secondary outcomes

Sonographic evaluation for lymphoceles is included in the discharge examinations. All results are noted in the discharge letter. Therefore, we have no doubt that assessing for “asymptomatic lymphocele at the day of discharge” will have high validity and reliability. The occurrence of “asymptomatic lymphocele,” “lymphedema,” “erysipelas,” and “rehospitalization” is included in the questionnaire mentioned above. Additionally, patients will receive the validated EORTC QLQ-C30 and the Lymphoedema Functioning, Disability and Health Questionnaire for Lower Limb Lymphoedema (Lymph-ICF-LL).

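### Asymptomatic lymphocele within 6 months is listed as a secondary outcome but defined by ultrasound; no study scan follows discharge, so it is not systematically ascertained

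*Protocol article*

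**What the plan says.** **Outcome.** The abstract (Methods/design) lists among the secondary outcomes "asymptomatic lymphoceles at the time of discharge and within 6 months of follow-up". The bulleted list under Secondary outcome measures differs: it names the asymptomatic rate at discharge only. The combined endpoint in that list also takes its asymptomatic part from discharge.

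**Definition.** Secondary outcome measures: "Asymptomatic lymphocele is defined as a sonographically detectable accumulation of fluid without symptoms".

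**Imaging.** The same section says that "ultrasonography will be performed by the assessors at the day of discharge", and that these assessors are blinded. The Table 1 row "Abdominal ultrasound" is marked at screening and at discharge, with no mark at 6 months. The Adherence section says that the sonographic checks are standard of care for all patients who have this operation with lymph node dissection.

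**Six months.** "Furthermore, we will conduct a follow-up 6 months postoperatively. We will contact the patient directly". Participant timeline describes questionnaires sent by email or post with yes/no answers only, completed by information from outpatient urologists. The Table 1 lymphocele row, covering symptomatic and asymptomatic, is marked at 6 months as well as at discharge. Under Data collection, Secondary outcomes, the occurrence of asymptomatic lymphocele "is included in the questionnaire mentioned above".

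**Symptomatic class.** The Primary endpoint section requires detectable fluid "with the need of an interventional or operative therapy due to one of the following symptoms".

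**The concern.** A man without symptoms cannot report a fluid collection that nobody has imaged. If he answers no at 6 months, he may have been scanned and found clear, or never scanned. The two answers look identical in the data, and the number of men actually examined is unknown in either arm. A 6-month comparison would then mix lymphocele formation with the amount of unscheduled imaging.

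The Discussion contrasts this trial with two ongoing trials that stop at 90 days. For asymptomatic lymphoceles the plan does not deliver the longer coverage that this contrast suggests.

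A related weakness sits in the two class definitions. One requires need for intervention and the other requires absence of symptoms, so they do not cover every visible lymphocele.

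**Working it through.** The plan gives no rate, effect or sample size for this outcome, so there is no figure to reproduce. The check sets the sections side by side.

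**1. Is the 6-month outcome declared?**

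| Place | Discharge | 6 months |
|---|---|---|
| Abstract, Methods/design | yes | yes |
| Secondary outcome measures, endpoint list | yes | no |
| Table 1, lymphocele row | yes | yes |
| Data collection, Secondary outcomes | yes | yes (questionnaire) |
| Table 1, ultrasound row | yes | no |

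Three places commit to collecting it. The endpoint list does not name it, and the ultrasound schedule does not support it.

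**2. Can another 6-month source replace the scan?** Outpatient urologists are named under Primary endpoint, in Participant timeline and in Table 1. No section requires them to scan. Data collection, Primary outcome, says that they are asked about the primary endpoint. Some cases may reach the trial through unscheduled scans, but neither the number of men scanned nor the method is fixed.

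**3. What would be missed?** Read the outcome as cumulative. Let d be the proportion detected at discharge, l the proportion arising later without symptoms, and s the fraction scanned after discharge.

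- True rate: d + l
- Recorded rate: d + s × l
- Shortfall: (1 − s) × l

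Only the later part is at risk, because every patient is scanned at discharge. The document gives neither l nor s. The Sample size section cites a 24.2% control rate for asymptomatic lymphocele within 90 days in another trial, without separating what was visible at discharge. As an illustration only, take d + l = 24.2% and assume s = 50%:

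- All visible at discharge (l = 0): shortfall 0.5 × 0 = 0 percentage points.
- None visible at discharge (l = 24.2%): shortfall 0.5 × 24.2 = 12.1 percentage points.

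A range of 0 to 12.1 points shows that the document cannot size the problem.

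**4. Do the classes cover every lymphocele?**

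| Lymphocele | Class | In combined endpoint? |
|---|---|---|
| Seen at discharge, no symptoms | asymptomatic | yes |
| Qualifying symptoms, intervention needed, within 6 months | symptomatic | yes |
| Seen at discharge with symptoms, no intervention needed | neither | no, unless later treated |
| Seen at discharge without symptoms, later untreated symptoms | asymptomatic at discharge | yes, already counted |
| Arises after discharge, symptoms untreated | neither | no |

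The third row is a patient with a lymphocele on the trial's own scan who is counted as free of the combined endpoint.

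**The case against.** The strongest reply is that the body already does most of what is asked. Its endpoint list uses discharge for both the asymptomatic rate and the combined endpoint, so no endpoint in that list depends on a 6-month asymptomatic rate. This stands, and it makes the repair small. It does not remove the abstract's statement, the 6-month mark in Table 1 or the questionnaire item.

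Secondly, a reader might infer that the outcome cannot be measured at all. The document does not support that, because outpatient urologists are a source and may find cases. What is missing is systematic ascertainment with a known denominator.

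Thirdly, a reader might infer that later scans follow complaints, or differ between arms, and so bias the comparison. No section says what prompts a scan after discharge, and patients and assessors are to stay blinded for 6 months. Differential scanning is possible but not shown.

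Fourthly, one might multiply a whole lymphocele rate by an assumed scan fraction and quote a loss of power. That ignores the discharge scan, which keeps everything detected there, and it rests on inputs the plan does not give.

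On the class gap, Secondary outcome measures says that lymphocele symptoms are assessed separately, so symptoms are recorded apart from treatment need. Requiring intervention in the primary definition is a legitimate choice. Both points are fair. The gap remains because the combined endpoint is built from the two classes, not from the symptom record.

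**Conclusion.** The point holds in a limited form. Asymptomatic lymphocele after discharge is not systematically ascertained: its definition needs a scan that the plan does not schedule, and the sections disagree on whether it is an outcome. The combined endpoint also omits lymphoceles seen at discharge with symptoms that need no intervention, unless they are treated later. Their number is not given and cannot be estimated from the document.

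The consequence is confined to one secondary outcome and one composite. The Statistical methods section makes all analyses other than the primary outcome exploratory. The primary endpoint, its sample size and the asymptomatic rate at discharge are untouched. It would go too far to conclude that these outcomes cannot show whether the flap prevents lymphoceles, since the discharge comparison rests on a blinded scan planned for every patient.

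The conclusion assumes that Table 1 is complete as shown and that no ultrasound after discharge is required elsewhere. It deserves correction before analysis, mainly to prevent an unreliable 6-month comparison from being reported.

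**What to change.** 1. Align the abstract, the Table 1 lymphocele row and the Data collection text with the endpoint list under Secondary outcome measures. Compare the arms on asymptomatic lymphocele at discharge only.
2. Add one yes/no item for patients and outpatient urologists: was an ultrasound of the pelvis done after discharge? Report later asymptomatic detections descriptively, with the number scanned in each arm as denominator.
3. Define the combined endpoint as any sonographic lymphocele at the discharge scan, whatever the symptoms, or a symptomatic lymphocele meeting the primary definition within 6 months. Do not extend it to untreated symptomatic lymphoceles arising after discharge, because confirming those would again depend on unscheduled scans.

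The cost is wording and one questionnaire item, with no added visit or imaging. One listed outcome becomes descriptive. Recruitment began in September 2019, so men enrolled early had passed their 6-month contact by submission in August 2020. For them the new item would need a further contact or be reported as unknown. The change should be recorded under the plan's own amendment procedure.

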**Discussion:**

The PELYCAN study is designed to assess whether the application of a peritoneal flap during RARP reduces the rate of symptomatic lymphoceles, as compared with the standard operation technique. In case of superiority of the intervention, this peritoneal flap may be suggested as a new standard of care.

**Trial registration:**

German Clinical Trials Register DRKS00016794. Registered on 14 May 2019.

**Supplementary Information:**

The online version contains supplementary material available at 10.1186/s13063-021-05168-x.

## Introduction and background

Pelvic lymphoceles present a common complication after RARP with lymph node dissection (LND) in approximately 10–18% of the cases [1–3]. Most lymphoceles are asymptomatic; nevertheless, in 1 to 15% of lymphoceles, symptoms occur. Obstruction of blood flow in the iliac vessels may cause thrombosis subsequently leading to venous thromboembolism. Hence, lymphoceles should be treated if they are symptomatic or impair venous blood flow. The current standard is percutaneous drain placement (ultrasound or computed tomography guided). However, in some cases, high flow rates of lymphatic fluid last for weeks thus causing substantial morbidity for the patient with additional hospital admission and loss in quality of life [1, 4–6]. In these cases, peritoneal fenestration is recommended [7].

To prevent lymphocele formation, especially lymphatic vessels at the level of the femoral canal are closed. For this purpose, different techniques have been introduced, which involve ligature, clipping, or mono- or bipolar sealing. However, these techniques are discussed controversially. On the one side, bipolar or monopolar coagulation may provide poor sealing of lymphatic vessels [8]. On the other side, no differences could be shown in a prospective randomized trial comparing clipping versus bipolar coagulation of lymphatic vessels at the level of the femoral canal [9]. However, these results are debated controversially [10, 11]. In addition, different approaches to reduce the rate of lymphoceles exist [12–15]. These strategies include intraoperative application of fibrin glue [12] or FloSeal® (Baxter International Inc., IL, USA), a hemostatic matrix that results in reduction of symptomatic lymphoceles [13]. However, the data regarding the clinical significance of hemostatic patches remains unclear, since the use of TachoSil® (Takeda Pharmaceutical Company Limited, Osaka, Japan) could not prove significant superiority [14]. Another study, which was assessing the benefits of using the Da Vinci® Vessel Sealer, a special endoscopic instrument by Intuitive Surgical (Sunnyvale, CA, USA), could not show a difference in the rate of postoperative lymphoceles (results not published on MEDLINE, ClinicalTrials.gov Identifier: NCT02035475). However, Yasumizu et al. indicated that using a vessel sealing device (EnSeal®, Ethicon Inc., Cincinnati, USA) can prevent the development of large lymphoceles. A difference in symptomatic lymphoceles could not be demonstrated [15]. Recently, published studies suggest that peritoneal fenestration or a peritoneal flap (PF) could decrease the risk for both asymptomatic as well as symptomatic lymphoceles due to resorption of lymph fluid by the peritoneum [6, 16–19]. In theory, this is caused by incision and folding over of the peritoneum into the region below of the field of the lymphadenectomy on both sides. This allows lymph fluid drainage from the true pelvis into the abdomen. On the one hand, the perivesical fat tissue no longer covers on the wound bed of the lymphadenectomy and lymph fluid can easily drain along the flap into the abdomen, and on the other hand, escaping lymph fluid can be reabsorbed via the peritoneum. Due to the methodical limitations of these studies (retrospective character, lack of randomization, insufficient statistical power), the efficacy of creating a PF remains unclear. In addition, in a recent study Bründl et al. report that implementation of a PF stays without effect on both symptomatic and asymptomatic lymphoceles [20]. However, in this trial sample, size calculation was based on the results by Lebeis et al. which might have been overoptimistic since a reduction to 0% is unlikely. At the time of submission, there are two further studies registered addressing lymphocele reduction after RARP by using a PF in a prospective setting (NCT03567525, DRKS00015720).

In conclusion, available evidence is limited and further high-quality RCTs are urgently needed.

Risk factors associated with lymphocele formation after RARP were identified in order to prevent imbalance between treatment groups. The following possible factors could be identified. However, evidence of most factors is controversially debated. The following possible factors could be identified or are under scientific debate:
While prophylactic treatment with low molecular weight heparin seems to be associated with a higher lymphocele incidence [21, 22], heparin dosage (prophylactic vs. bridging) seems not to affect lymphocele rates [23]. Controversially, other data suggest no association between the formation of lymphoceles and prophylactic heparin regimen [24].A higher lymph node count has been shown to be predictive of a higher incidence of symptomatic lymphoceles [3, 22, 25, 26]. Furthermore, extended LND has been associated with a longer hospital stay [3] and a higher risk of lymphorrhea [26]. On the other hand, there is data, which suggests no association between node count and lymphoceles [27, 28].Diabetes mellitus seems to be associated with lymphocele development in general [29, 30] and was showed to be significantly associated with a higher risk of developing a superinfected post-prostatectomy lymphocele [31].Patients with symptomatic lymphoceles after RARP could be associated with a significant lower body mass index (BMI) [25].The use of either metallic clips or electrocoagulation could not be associated with a difference in lymphocele incidence after RARP so far [9].Drain placement seems not to affect the incidence of symptomatic lymphoceles [32].An age of > 65 years has been identified as a significant predictive marker for the occurrence of symptomatic lymphoceles [26].

### Objective and hypothesis

The aim of the PELYCAN study is to provide reliable evidence of the effectiveness of creating a PF after transperitoneal RARP with LND. The null hypothesis that will be tested in a confirmatory analysis is that the rate of symptomatic lymphoceles will be the same in both treatment groups or better in the control group.

## Methods

### Design

The PELYCAN study is a parallel-group, patient- and assessor-blinded, phase III, adaptive randomized controlled superiority trial with a 1:1 allocation ratio. The primary endpoint is the rate of symptomatic lymphocele 6 months after surgery.

### Study setting

The study will be performed at a tertiary university care center (University Medical Center Mannheim, Heidelberg University) in Germany. The study starts single-centered. Additional centers might be initiated during the trial. The country of recruitment and thereby data collection will be Germany. The study will be conducted according to the SPIRIT (Standard protocol items: Recommendations for Interventional Trials) Initiative [33] and CONSORT [34] guidelines. This study protocol follows the recommendations of the SPIRIT checklist [33]. The checklist has been included as Additional file 1.

### Trial population

All adult patients with an indication for elective transperitoneal RARP with regional or extended pelvic LND due to biopsy confirmed PCa will be screened for eligibility.

### Eligibility criteria

Patients must provide written informed consent before study participation (see Additional file 2 for sample informed consent form).

#### Patient inclusion criteria

Patients must
(1) be newly diagnosed with histologically confirmed and clinically localized PCa and have chosen for laparoscopic, robotic-assisted radical prostatectomy (RARP)(2) provide mental capacity to consent(3) be at least 18 years old(4) be able to read and speak German

#### Patient exclusion criteria

(1) previous laparoscopic inguinal hernia repair with mesh implantation(2) previous pelvic radiotherapy or major pelvic surgery(3) poor German language skills(4) metastasized disease(5) previous history of head injury, dementia, or psychiatric illness

### Interventions

#### Intervention description

Both groups receive standard transperitoneal RARP with pelvic LND. Whereas one group is attributed to the intervention (group A = PELYCAN), the other group (group B = control) will be the control group.

##### Group A: Intervention = PELYCAN

Following, the standard operative technique is described. Small variations according to the surgeon’s preference, such as the order of the right- and left-sided lymphadenectomy or using clips during lymphadenectomy and their amount, are allowed but must be recorded in the operation protocol. Radical prostatectomy will be performed by experienced high-volume surgeons. All surgeons use the same steps for LND, RARP, and the same vesicourethral anastomosis technique. The da Vinci® Xi Surgical System is used to perform the procedures.

Patients are under general anesthesia. The patient is placed in approximately 45° Trendelenburg position. Both arms are placed along the body. In total 6 trocars are placed in a modified, semicircular fashion (Fig. 1): 4 da Vinci® trocars (supraumbilical (8 mm trocar), left and right to the umbilicus (two 8 mm trocars), lower left hemiabdomen (8 mm trocar)) and 2 assistant trocars (right lower (11 mm trocar) and right upper (5 mm trocar) abdomen). Diagnostic laparoscopy is used to identify peritoneal adhesions prior to trocar placement. Peritoneum is incised next to the medial umbilical ligament. Next, the urachus is ligated, followed by preparation of the retropubic space down to the symphysis, which fully mobilizes the urinary bladder. Lateral umbilical ligament is incised to the spermatic duct on the left side. The procedure is repeated at the contralateral side (Fig. 2b). Afterwards, pelvic lymph node dissection is performed: The right internal inguinal ring is identified, followed by preparation of the lymph-node containing tissue in the obturator fossa between the external iliac vein and the obturator nerve. If assessed necessary by the surgeon, titanium clips (AESCULAP® Challenger® Ti-P, B. Braun, Melsungen, Germany) are used. In high-risk PCa extended LND (lateral margin: external iliac artery, cranial margin: bifurcation of the iliac artery) is performed. Lymph node dissection is performed at both sides. Lymph node tissue is placed in the ExBag® (ASID BONZ, Herrenberg, Germany) specimen pouch. After incision of the endopelvic fascia, the prostate is mobilized and suture ligation of the dorsal venous plexus is performed using one 4/0 Vicryl (Ethicon Inc., Cincinnati, USA) running suture. Bladder neck preparation is done in gentle technique with anterior incision.

